**Figure 1 F1:**
[figure not shown]
Flow-chart WoPaCom study.

### Setting and recruitment

The study takes place at an occupational health service which performs periodical preventive medical check-ups once every four years. For the current study, two questionnaires were added in order to screen for symptoms of chronic fatigue and symptoms of depression.

The CIS-20 (Checklist Individual Strength) is a 20-item self-administered questionnaire and measures several aspects of fatigue being subjective feeling of fatigue, concentration, motivation, and physical activity [24,25]. The items are scored on 7-point Likert scales (1 = “Yes, that is true”, to 7 = “No, that is not true”). Higher scores indicate a higher degree of fatigue, more concentration problems, reduced motivation, and less activity. A cut-off point of >76 was used to define fatigue in a working population [26].

The PHQ-9 (Patients Health Questionnaire) consists of nine questions regarding the prevalence and intensity of symptoms of depression over the last two weeks. The response options are: “Not at all”, ”Several days”, “More than half the days” and “Nearly every day”. Its brevity and the fact that it is a self-administered questionnaire make it a useful tool in screening for depression in primary care. The PHQ-9 has been validated for both diagnosing depression and measuring severity [27-29] and even for evaluating treatment effects [30,31]. All participants who scored at least two depressive symptoms at least at “more than half the days” and at least one of these symptoms was depressed mood or anhedonia, were eligible. Depressed mood was present with a PHQ score of >4 (mild depression), but <20 (moderately severe depression) [32].

Workers with heightened scores of either fatigue and/or depressed mood were invited for an additional diagnostic interview to confirm their eligibility and to check for exclusion criteria. The Mini International Neuropsychiatric Interview (MINI) was used to confirm the diagnosis from the PHQ-9. The interview was administered by a trained nurse. The MINI is a validated and reliable diagnostic structured interview covering 17 disorders based on DSM-IV criteria [33,34]. A visual analogue scale was also used to determine the negative impact of the complaints on daily life functioning (ranging from 0 (no impact) to 100 (extreme impact)). A cut-off point of 30 was arbitrarily chosen. Participants were excluded if the MINI indicated a major depression in combination with a PHQ-9 score of 14 or higher, in case of recent (medical) events as an explanation for fatigue, serious psycho-social problems, former episodes of depression or bipolar disorder or psychiatric co-morbidity, passive death wish or suicidal thoughts, and alcohol or drug dependency (Table 1). If participants met the criteria for fatigue and depressed mood, exceeded the score of 30 on the impact visual analogue scale they were asked for informed consent. Serious psychiatric conditions would have been referred further (e.g. to physician), but this did not occur in our study.

**Table 1 T1:** Inclusion and exclusion criteria as applied by the occupational nurse

**Inclusion criteria:**	**Exclusion criteria:**
- Score PHQ-9 > 3 < 14	- Severe / major depression
- Score CIS-20 > 76	- Major psychiatric problems ( e.g. bipolar depression, schizophrenia, suicidal risk)
- Burden in daily life > 30 (visual analogue 0–100)	- Current psychological/psychiatric treatment
	- Relevant clinical disease
	- (Drug) Addiction(s)
	- Recent (life) events strongly related to fatigue and depression (e.g. recent (major) surgery)

### Randomisation

After having completed the baseline questionnaire, participants were randomly assigned to either the intervention or control group to ensure equal numbers in both groups. Furthermore, the randomisation was stratified to avoid possible confounding. The strata are the customer organization (representing different production plants and organisational structure), income (low, high as defined by the median income in the organization), and gender (male, female). The intervention group received the Minimal Psychological Intervention. The control group received care as usual, being the standard follow-up by the occupational health physician. Mostly this consists of additional consultation and follow-up advice. The principles underlying the intervention (cognitive behavioural therapy and self-management) have been validated in previous research [35,36] and we therefore think that our findings are not substantially biased by the Hawthorne effect. All possible co-interventions were registered in both intervention as well as control group.

### Minimal Psychological Intervention

The intervention was carried out by a trained occupational nurse. During a period of at most four months, participants assigned to the study group had a minimum of 1 and a maximum of 10 consultations with the nurse. All consultations took place on an individual basis. There were no group sessions. The number of and time between visits depended on the participant’s progress and was thus tailor-made. The Minimal Psychological Intervention contains elements from the Chronic Disease Self-Management Program (CDSMP) by Lorig and Gonzales [37], the Reattribution model from Goldberg [38] and from the work of the project group of the Interventie Studie Eerste Lijn (INSTEL) [39]. The intervention aims at teaching workers to take responsibility for day-to-day management of their problems and its consequences for daily functioning.

The MPI consists of five phases: Phase 1: The nurse explores the participants’ cognitions on the origin of symptoms and complaints, and their relation to limitations and behaviour. Phase 2: The participant keeps a diary, where he or she records symptoms, complaints, thoughts, worries, related feelings, and behaviour. Phase 3: Using information from the diary, the nurse challenges the participant to link his behavioural strategies to his or her complaints. Phase 4: Introduction of the self-management approach by the nurse. The participant explores his or her possibilities to alter his or her behaviour. He or she then makes a plan on how to solve perceived problems and sets specific goals to be reached before the next consultation with the nurse. Phase 5: Evaluation of the progress in achieving the goals.

After a participant has completed these five phases successfully, he or she is supposed to be able to apply the self-management approach to any situation or problem he or she may encounter in the future. Nurses performing the diagnostic interview with a particular participant did not perform the MPI in that particular participant.

### The training program for nurses

During four 8h sessions, with 2-week time intervals, and the last with a four-week-interval, five nurses were trained by experienced trainers (a behavioural scientist with experience in cognitive behaviour therapy, a psychiatrist and a pharmacist) on how to apply both the diagnostics as well as the intervention. In between training days, nurses practised their newly learned skills on a pilot patient. At the end of training, two of the nurses who showed the most affinity with and best availability for performing the MPI were selected to participate in the intervention. As mentioned earlier, the training program has previously shown to be feasible, attractive and successful among nurses [18-20], but is evaluated again in the current study. Booster sessions were held monthly during the first part of the study and then gradually scaled down depending on the specific needs of the nurses; both a psychiatrist and a psychologist could be contacted by telephone to discuss cases at any time.

### Data collection

Data are collected at four points in time: at baseline (T0), one week after the intervention period (T1), and at six and twelve months after the intervention period (T2, T3) (Figure 1). The intervention period for participants allocated to the intervention group varies from one week to four months. T1 (the first follow-up phase) for the control group was set at 4 months, which was the estimated mean duration of the intervention period in the intervention group. Data were collected using self-administered questionnaires (Figure 1). Workers and nurses allocated to the intervention group were well aware of the allocated arm. Randomisation and data collection was carried out by separate administrative personnel members without any competing interests.

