## Design and methods

### Design

WoPaCoM is a study conducted in an Occupational Health Service in the South of The Netherlands that started at the end of 2007. Data gathering was finished in 2012. The customers of this service have their activities in the chemical industry. The two main customer organizations consist of approximately 6,000 workers in several settings, jobs and positions, varying from white and blue collar workers to researchers and administrative personnel. The WoPaCoM study is a two-armed (stratified) randomised controlled trial (with a block size of 4), evaluating the effectiveness of the MPI, including a process evaluation, for decreasing symptoms of fatigue and depression. After the baseline measurement, follow-up measurements at 4, 6 and 12 months are carried out (Figure 1). A total number of 124 participants will be included. The effect of MPI will be compared with care as usual. The ethics committee of the Maastricht University Medical Center found that the study was not subject to the Dutch Medical Research Involving Human Subjects Act (WMO): subjects were not subjected to invasive treatments, the subjects’ privacy was sufficiently guaranteed, and the setting was one in which regular occupational care was evaluated.

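### T1 is timed by a different rule in each arm, on a rationale the protocol contradicts, and T2/T3 have two incompatible definitions, so the T1 contrast, and possibly the later ones, mixes treatment with elapsed time

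*Protocol article*

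**What the plan says.** The timing of follow-up is described in four places in the protocol article.

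- **Data collection, MPI arm.** The first follow-up is "one week after the intervention period (T1"), and "The intervention period for participants allocated to the intervention group varies from one week to four months".
- **Data collection, control arm.** "T1 (the first follow-up phase) for the control group was set at 4 months, which was the estimated mean duration of the intervention period".
- **Data collection, later visits.** These fall "at six and twelve months after the intervention period (T2, T3"). No separate origin is given for controls.
- **Design.** "After the baseline measurement, follow-up measurements at 4, 6 and 12 months are carried out". The Abstract gives the same 4, 6 and 12 months. Neither place distinguishes the arms.

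The Minimal Psychological Intervention section adds that consultations take place "During a period of at most four months", and that "The number of and time between visits depended on the participant’s progress and was thus tailor-made".

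The Analysis section names a multilevel repeated measures analysis, adjusted for baseline differences, age, gender and socioeconomic status. It does not state how time enters the model.

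**The concern.** The primary outcomes, CIS-20 and BDI, are compared between arms at follow-up. If the arms are measured at different times since baseline, the contrast contains the treatment effect plus whatever change belongs to the extra or missing months: natural recovery, regression to the mean, or waning of an early effect. Randomisation does not remove this, because the difference in timing is created after randomisation by the measurement rule itself.

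Two features make it more than a nuisance. First, treatment length in the MPI arm follows progress, so the date of T1 is linked to the outcome being measured. Second, the only reason offered for treating the two T1 dates as comparable is that 4 months is the average treatment length, and this conflicts with 4 months being the upper limit.

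For T2 and T3 the problem is a contradiction: the reader cannot tell which months are being compared, or from what point controls are counted.

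**Working it through.** **Inputs.** Treatment period D in the MPI arm: 1 week to 4 months (Data collection; the upper limit also in the Minimal Psychological Intervention section). T1 in MPI: D plus 1 week. T1 in control: 4 months. One week = 7/30.44 = 0.23 month. Planned decreases: 25% against 5% (Power calculation). MPI times below count from the start of the treatment period; they equal time from baseline only if treatment starts at baseline, which the article does not say.

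**1. The plan's own figures.** The sample size reproduces as a comparison of two proportions with unpooled variance, two-sided α 0.05 and power 0.90:

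(1.960 + 1.282)² × (0.25×0.75 + 0.05×0.95) / 0.20² = 61.7, so 62 per arm; 62 / 0.75 = 82.7, so 83.

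It is not in dispute. The match suggests that the 20-point difference may be one between proportions rather than a percentage of baseline score, which limits any comparison with step 5.

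**2. Mean against maximum.** If no D exceeds 4 months, the mean of D is 4 only when every D is 4. A period that varies down to one week, with visits set by progress, does not fit that.

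**3. T1.**

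- Earliest MPI T1: 0.23 + 0.23 = 0.46 month. Against control: 0.46 − 4 = −3.54 months.
- Latest MPI T1: 4 + 0.23 = 4.23 months. Against control: +0.23 month.
- Average, assuming D is uniform over the stated range: mean D = (0.23 + 4)/2 = 2.11; mean T1 = 2.34; gap about 1.7 months.
- If D clusters at 4 months, the average gap is close to zero. Any lag between baseline and the first consultation moves MPI T1 later, which shrinks the 3.5-month and 1.7-month figures.

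**4. T2 and T3.** On the Data collection wording, MPI is measured at D + 6 = 6.2 to 10.0 months and D + 12 = 12.2 to 16.0 months.

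| Reading | MPI (T2; T3) | Control (T2; T3) | MPI relative to control |
|---|---|---|---|
| Data collection, controls counted from month 4 | 6.2–10; 12.2–16 | 10; 16 | 3.8 months earlier to 0 |
| Data collection for MPI, Design for controls | 6.2–10; 12.2–16 | 6; 12 | 0.2 to 4.0 months later |
| Design for both arms | 6; 12 | 6; 12 | 0 |

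Both the presence and the sign of the gap depend on the reading.

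**5. Illustrative size at T1.** Assume the planned 5% control decrease is natural change, linear over H months.

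- H = 4: 5/4 = 1.25 points per month. A 1.66-month gap is worth 2.1 points; a 3.54-month gap, 4.4 points.
- H = 12: 5/12 = 0.42 point per month. The same gaps are worth 0.7 and 1.5 points.

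**The case against.** The best defence is that measuring just after treatment ends is a recognisable choice, that the Abstract and the Design section give one schedule for both arms, and that a multilevel model can handle unequal timing. Parts of this stand.

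- **Every contrast is affected.** A reader might infer this. The text supports it outright only for T1, where Data collection sets arm-specific rules. At T2 and T3 the gap is zero if the Design schedule governs both arms. The flow chart is not shown and might settle the origins, although it could not remove the conflict in the text. Sick leave comes from plant registrations and need not follow questionnaire dates.
- **The model uses visit labels instead of dates.** The article does not say so. Coding of time is commonly left to the analysis plan, and its absence is not the fault here. The fault is the stated schedule.
- **The bias is large.** A natural decline of 1–2% per month would give 1.7 to 3.3 points for the 1.7-month gap, but it would also imply a 12–24% fall in controls over 12 months, against the planned 5%. The documents do not support that rate. The uniform spread of durations is likewise an assumption, and it sets aside the only central value that the article gives.
- **The bias favours MPI.** Not established. Earlier measurement with natural recovery works against MPI at T1; measurement just after treatment ends works for it.

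What the defence does not answer is that Data collection gives the arms different T1 rules, that its rationale clashes with the stated maximum, and that its T2/T3 definition cannot be squared with the Design section.

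**Conclusion.** The point holds in a limited form. At T1 the arms are on different clocks by rule: MPI between about 3.5 months earlier and 0.2 month later than control, counted from the start of treatment. The justification by average duration conflicts with the article's own upper limit. At T2 and T3 the definitions contradict each other, and the gap ranges from 3.8 months earlier to 4.0 months later in MPI, or is nil, according to the reading.

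The T1 contrast, and possibly the T2 and T3 contrasts, therefore mixes treatment with elapsed time, in a direction that cannot be fixed in advance. The figure of 0.7 to 2.1 percentage points at T1 is illustrative only. It rests on uniform durations, treatment starting at baseline, and a linear 5% control decrease over 4 to 12 months. The sample size is unaffected.

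**What to change.** 1. Reconcile the T1, T2 and T3 definitions in the Abstract, the Design section and Data collection, and state one origin, baseline or randomisation, for both arms.
2. Reconcile the description of 4 months as an average with its description as an upper limit. The documents do not show which is meant.
3. If completion dates were recorded, which the article does not state, enter actual time from randomisation to questionnaire completion in the multilevel model. Estimate the between-arm difference at elapsed times that data in both arms support, for example 12 months.
4. Report the contrasts by nominal T1, T2 and T3 as a sensitivity analysis.

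Data collection is finished, so only wording and analysis can change. The cost is a few extra model parameters, slightly wider intervals, and some interpolation at 4 months for participants who finished early. On the Data collection schedule, 12 months is also interpolated between T2 and T3 in the MPI arm. Because MPI timing follows progress, modelling actual time reduces the bias without fully removing it. That should be stated as a limitation when results are reported.

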### Effect evaluation

Table 2 provides an overview of the outcome measures. The primary outcome measures in this study are fatigue as measured with the CIS-20 and the level of depression as measured with the Beck Depression Inventory (BDI) [40,41]. Secondary outcome measures in the study are quality of life as measured with the SF-36 [42], Mastery using the Personal Mastery Scale developed by Pearlin and Schooler [43], and General Self Efficacy [44,45]. Sick-leave data were available from official plant registrations. Varying covariates were measured. Information on demographic factors (age, gender, marital status, religion, education, occupation, and income) was collected in the screening phase. Other measures were coping using the active coping, avoidant coping and passive coping scales from the Utrecht Coping List (UCL) [46], anxiety assessed using the anxiety subscale from the Symptom Checklist (SCL-90) [47], co-morbidity using a 24-item chronic conditions list (e.g. heart disease, cancer) and 16-item life-events list where patients report which life events they have experienced in the past year, and how they value these events (positive, negative, or neutral). To check for contamination in the control group, two questions are added in the T3 questionnaire asking whether or not workers in the control group had heard, used parts of, or somehow benefited from the MPI.

**Table 2 T2:** List of instruments (questionnaires/variables)

**Variable/ used instrument**	**Moment in time**				
	**PMCU***	**T0**	**T1**	**T2**	**T3**
Organization	X				
Income	X				
Gender	X				
Age	X				
PHQ-9 [27-29]	X	X			
CIS20 [25,26]	X	X	X	X	X
SF-36 [40]		X	X	X	X
BDI [38]		X	X	X	X
SCL (Anxiety scale) [40]		X	X	X	X
UCL [44]		X	X	X	X
Pearlin & Schooler Mastery [41]		X	X	X	X
Sherer/Bosker (GSE) [42]		X	X	X	X
Prodisq (module C-E) [46,47]		X	X	X	X
Chronic disease		X			X

*PMCU Periodic Medical Check Up.

### Economic evaluation

For an economic evaluation, several modules of the PROductivity and DISease Questionnaire (PRODISQ) were used for the measurement of productivity costs. The modular questionnaire covers all relevant aspects of the relationship between health and productivity. In this study we will concentrate on productivity of individual participants. We used several PRODISQ modules including absence from work (module C), compensation mechanisms that may reduce productivity loss (module D), and reduced productivity at work (module E) [48,49]. Absence from work is measured as the total number of lost working days as well as the number of sick-leave episodes within a period of three months. Compensation mechanisms include the compensation of sick leave days by either the worker himself or a colleague, with or without extra productivity cost. Productivity cost being differentiated in the amount of work and the quality of work.

### Analysis

Data will be analysed according to the intention to treat principle. Despite participants dropping out of the intervention or not returning follow-up questionnaires, each individual is analysed as randomized (either control or intervention). We tried to encourage (potential) drop-outs to return their questionnaires in order to have complete data as much as possible. But if this was not possible, available (but not complete) data will still be included in the multilevel repeated measures analysis; this type of analysis better allows incomplete data. Finally, in the forthcoming articles, we will give full insight into the response rates at all phases of the study and consideration of the extent to which this might have caused specific biases.

Changes in primary and secondary outcome measures between the intervention and the control group will be analysed using both univariate and multivariate techniques. Models will be adjusted for baseline differences, age, gender, and socioeconomic status. Potential additional confounding factors and effect modifiers (covariates) will be checked separately and when necessary included in the model. If numbers permit, subgroup analyses will study the robustness of the findings across organizations and workers with a low and high income.

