**Methods/design:**

The presented WoPaCoM study (Work Participation of Workers with Common Mental complaints) is a two-armed randomized controlled trial, comparing MPI with usual care. A total number of 124 workers suffering from (chronic) mental fatigue or mild to moderate depression will be included. A stratified and block randomization will be applied, stratifying by customer organisation, income, and gender, using a block size of four. It will include a baseline measurement and subsequently follow up measurements after 4, 6 and 12 months. The primary outcome measures are symptoms of either fatigue (using the Checklist Individual Strength) and/or depression (using the Beck Depression Inventory) and secondary outcome measures include sickness absence, self efficacy, costs and quality of life. Analysis will include both univariate and multivariate techniques and data will be analysed according to the intention to treat principle.

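### Customer organisation stratifies the randomisation but is missing from the fixed covariates, and socioeconomic status is not tied to the randomised income stratum (minor, free to fix)

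*Protocol article*

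**What the plan says.** **Allocation.** The abstract describes the randomisation as "stratifying by customer organisation, income, and gender, using a block size of four". The Randomisation section gives the factors: "The strata are the customer organization (representing different production plants and organisational structure"), then "income (low, high as defined by the median income in the organization), and gender (male, female"). The reason given is that "the randomisation was stratified to avoid possible confounding". The Design section implies two levels for the organisation factor: "The two main customer organizations consist of approximately 6,000 workers in several settings, jobs and positions".

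**Analysis.** The fixed covariates are given in one sentence: "Models will be adjusted for baseline differences, age, gender, and socioeconomic status". The next sentence opens a conditional route: "Potential additional confounding factors and effect modifiers (covariates) will be checked separately and when necessary included in the model". Organisation is named in this section only for optional work, to be done if there are enough participants: "subgroup analyses will study the robustness of the findings across organizations and workers with a low and high income".

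**Definitions.** Socioeconomic status is not defined. The Effect evaluation section lists education, occupation and income among the demographic items, and any of them could be meant. Table 2 shows organisation, income and gender recorded at the periodic check-up.

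**The concern.** Blocking within strata balances the arms on the stratifying factors. Where those factors predict the outcome, this reduces the true sampling variance of the treatment effect. A model that leaves them out keeps their contribution in the residual variance, so its standard error does not reflect that reduction. Confidence intervals are then wider than they need be, and the test rejects less often than its nominal level.

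The article has its own reasons to think organisation may matter. It describes the factor as standing for different plants and structures, stratifies on it to avoid confounding, and plans subgroup analyses by it. Yet it gives the factor no main effect in the fixed model.

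For income the gap is one of definition. The randomised factor is income relative to the median in the worker's own organisation. If medians differ between organisations, an absolute measure of socioeconomic status, with no term for organisation, does not reproduce that factor.

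At stake is a small amount of precision and a slightly conservative test.

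**Working it through.** **1. The lists side by side**

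| Stratification factor | In the fixed covariates? |
|---|---|
| Gender | Yes, by name |
| Income, low/high at the organisation's median | Unclear: socioeconomic status is named but not defined |
| Customer organisation | No |

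**2. The plan's own figure.** The Power calculation section gives α = 0.05, power 0.90, 25% against 5%, and 62 per arm. As two proportions, two-sided, with unpooled variance:

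n = (1.960 + 1.282)² × (0.25 × 0.75 + 0.05 × 0.95) / 0.20² = 10.507 × 0.235 / 0.04 = 61.7, so 62.

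With 25% attrition, 62 / 0.75 = 82.7, so 83. Both figures reproduce. The calculation uses no covariates, so this point does not change the required number.

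**3. Effect of leaving the strata out.** Let r be the share of outcome variance explained by the omitted strata *after* the named covariates. The documents do not give r, so 0 to 0.10 is an assumed range. Set the model standard error without strata to 1; the true standard error is then √(1 − r). Take the effect that gives 90% power at standard error 1, which is 1.960 + 1.282 = 3.242 standard errors.

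- Ratio of model to true standard error: 1/√(1 − r)
- True type I error: 2Φ(−1.960/√(1 − r))
- Power, strata omitted: Φ(1.282/√(1 − r))
- Power, strata included: Φ(3.242/√(1 − r) − 1.960)

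| r (assumed) | SE ratio | True type I error | Power omitted | Power included | Loss (points) |
|---|---|---|---|---|---|
| 0 | 1.000 | 5.0% | 90.0% | 90.0% | 0 |
| 0.01 | 1.005 | 4.9% | 90.1% | 90.3% | 0.2 |
| 0.02 | 1.010 | 4.8% | 90.2% | 90.6% | 0.3 |
| 0.05 | 1.026 | 4.4% | 90.6% | 91.4% | 0.8 |
| 0.10 | 1.054 | 3.9% | 91.2% | 92.7% | 1.6 |

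Example, r = 0.10: √0.90 = 0.9487. Type I error is 2Φ(−2.066) = 3.9%. Power is Φ(1.351) = 91.2% omitted and Φ(1.457) = 92.7% included.

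**4. Simulation check.** There were 124 participants, two organisations, 7% women, stratified blocks of four and 3,000 runs per setting. A linear model with baseline, gender and continuous income (standing in for socioeconomic status) was fitted with and without organisation and the income stratum. Residual SD was 0.85, the treatment effect 0.5, and the income-stratum effect half the organisation effect. All of these are assumptions.

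| Organisation effect | Mean SE, omitted / included | Power, omitted / included | Type I error, omitted / included |
|---|---|---|---|
| 0.2 | 0.1544 / 0.1540 | 90.6% / 90.7% | 0.050 / 0.050 |
| 0.6 | 0.1616 / 0.1541 | 87.3% / 89.7% | 0.041 / 0.051 |

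The larger setting corresponds to r ≈ 1 − (0.1541/0.1616)² = 0.09, near the top of the range. Its power gap of 2.4 points exceeds the step 3 figure partly because the simulation holds the *adjusted* power near 90%. On that footing, step 3 at r = 0.10 gives Φ(3.242 − 2.066) = 88.0%, a loss of 2.0 points. Direction and order of size agree.

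**The case against.** **Income may already be covered.** Income is a usual component of socioeconomic status, and the same paragraph of the Analysis section speaks of low and high income. This stands. A reader might infer that the model adjusts for neither organisation nor income, but the documents do not support that. They show that organisation is absent from the fixed list and that socioeconomic status is undefined.

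**Organisation could enter later.** The conditional clause allows further covariates when necessary, so the route exists. It is a weak one, because the check is for confounding and stratified blocking balances organisation by design. The Progress of the study section itself reports equal arm numbers within strata. Such a check would tend to leave organisation out, whereas the reason to include it is a correct standard error. The decision would also depend on the data.

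**The loss may be negligible.** What counts is the variance explained beyond baseline score, age, gender and socioeconomic status, and that may be 1% to 2% or nothing. This stands. It is tempting to say flatly that the standard errors are too wide, but without a value for r that is conditional.

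**The gain is easily overstated.** A reader might compare 90% with the adjusted 91.4% or 92.7% and read off a gain of up to nearly 3 points. That ignores the fact that the analysis without strata already benefits from the stratified allocation: its power is 90.6% or 91.2%.

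**Power is not visibly short.** The design aims at 90%, and 127 participants completed follow-up questionnaires against 2 × 62 = 124 required. This stands, and nothing here suggests that the trial is underpowered.

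**A condensed article.** Exact model terms are often left to a fuller document. But this article does state its fixed covariates, and that list does not match its own stratification.

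**Conclusion.** The mismatch is real and minor. One of the three stratification factors, customer organisation, is absent from the fixed covariates. A second, income, is covered only if socioeconomic status happens to mean the randomised stratum.

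For an assumed residual share r of 0.01 to 0.10, model standard errors are about 0.5% to 5% too wide, the true type I error is about 4.9% to 3.9%, and the power loss is about 0.2 to 1.6 points. At r = 0 there is no loss. The figures rest on r, which the documents do not give, and on a normal approximation.

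The error is on the conservative side. A reader might infer a biased treatment effect, but randomisation balances the strata and omitting them does not shift the estimate. Dropout that differed by organisation could disturb that balance among those analysed, but the documents report none. Nor do they say that stratification was meant to buy precision; the stated purpose is to avoid confounding.

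Label: free improvement, minor.

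**What to change.** State in the Analysis section, before the outcome data are analysed: *All effect models include, as fixed main effects, the T0 value of the outcome, customer organisation, the low/high income stratum as used in randomisation, gender and age.* Organisation then no longer depends on the confounder check. If socioeconomic status is meant to cover more than that income stratum, say how it is measured and list it separately.

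Use main effects, not the full cross of strata. With 7% women, 124 to 166 participants (2 × 62 to 2 × 83) include about 9 to 12 women (0.07 × 124 = 8.7; 0.07 × 166 = 11.6). Over four female strata (two organisations by two income levels) that is about two or three each.

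The cost is one sentence and one or two degrees of freedom, assuming two organisations. The stratum variables were recorded at the check-up, so nothing new is collected, and the sample size does not change.
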